## Discussion

This study explores the use of escalating doses of donor-derived anti-leukemia CTL to prevent leukemia relapse in high-risk pediatric patients affected by acute leukemia and given haplo-HCT. The primary objective is the incidence of acute GVHD compared with that observed in a control cohort of patients with identical characteristics, treated with infusion of unmanipulated DLI. Haplo-HCT based on selective depletion of TCRα/β+ and CD19+ cells has been increasingly used in pediatric patients affected by high-risk acute leukemia. By this kind of graft manipulation, T cells expressing the αβ chains of the T cell receptor, which are responsible for the development of GVHD, are removed with a high depletion efficiency (36). However, the almost complete elimination of T cells on the graft increases the risk of infections and relapse. Infusion of donor-derived mature T cells represents a way to overcome these complications. Over the years, several strategies of donor-T cell manipulation prior transfer in patients have been proposed to improve the outcome of patients without the emergence of acute and chronic GVHD that represent the most common complications after DLI. Results of clinical trials documented that the transfer of selective populations of mature T cells may improve the recovery of pathogen-specific immunity but there are no significant data regarding the incidence of relapse (37, 38).

Anti-leukemia CTLs obtained by stimulation with patients’ LB are specific for each individual blast signature, and, due to their physiological recognition and effector mechanism through their natural T cell receptor, exert leukemia-specific killing with less severe adverse reactions than CAR-T cells. In addition, their potential to recognize multiple leukemia-associated antigens present on the blast surface should make them less susceptible to immune evasion strategies developed by leukemic cells. Additionally, the risk of GVHD should be reduced by the culture procedure, which decreases the number of alloreactive T cells. For these reasons, the use of these T cells after HCT in a highly personalized approach may be a safer and more effective option than unmanipulated DLI to prevent leukemia relapse after HCT. To support this hypothesis, in a pioneer study performed in patients treated on a compassionate basis, we documented that the infusion of large numbers of anti-leukemia CTL is safe, as no patient experienced acute or chronic GVHD or severe immune adverse reactions, and may contribute to the restoration of CR in a proportion of patients relapsing after the allograft. In case of overt clinical relapse, prior reduction of the tumor burden may facilitate the anti-leukemia effect displayed by CTLs (39).

Overall, the results of this clinical study may open the way to a new approach, different from CAR-T cell therapy, for the management of high-risk patients given haplo-HCT. Overall, analysis of the features of ATMP produced so far documented that there is a certain degree of homogeneity in terms of potency and surface markers among ATMP batches in different donors and among batches produced from the same donor. Batches from different donors could show variability in lytic capacity always within the acceptable release criteria range. The evaluation of immunological properties of the infused anti-leukemia CTL and clinical follow up of treated patients could allow a better understanding of how the functional and phenotypical CTL characteristics may affect patients’ outcome.

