## Methods and analysis

### Trial design

Leuk-001 is a Phase I/II, monocentric, open label, non-randomized, prospective clinical trial of donor-derived anti-leukemia CTLs in pediatric haplo-HCT recipients transplanted for ALL or AML and with a risk of leukemia relapse after haplo-HCT ≥ 50%. The outcome of treated patients will be compared with that of pediatric recipients of haplo-HCT with the same disease characteristics and prognosis, who received infusions of unmanipulated DLI. Patients will be assigned to the treatment with anti-leukemia CTLs (experimental arm) or to standard treatment with DLI (control arm) based on the availability of cryopreserved viable LB collected at the diagnosis or at relapse, necessary for the production of anti-leukemia CTLs (**Figure 1**). Therefore, this will be the only difference between the study population and the control population.

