**Figure 1 f1:**
[figure not shown]
Trial design flow chart. The study population includes high-risk ALL or AML pediatric patients candidate to haplo-HCT and with an expected risk of leukemia relapse after transplantation ≥ 50%. The donor, once screened and deemed eligible, will undergo leukapheresis to obtain PBMC cryopreserved in multiple vials. Depending on the availability of cryopreserved LB patients will be assigned to the treatment with anti-leukemia CTLs (experimental arm), otherwise they will proceed to standard treatment with DLI (control arm).

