### Study objectives

The primary objective will be safety, measured as the incidence of acute GVHD after treatment. Acute GVHD will be diagnosed and graded according to the NIH criteria. Grade II-IV acute GVHD will be expressed as cumulative incidence considering disease relapse and death in remission without GVHD as competing events. The key secondary objective will be preliminary efficacy, measured as the incidence of relapse, (REL) defined as the time from HCT to the date of disease relapse, will be calculated at 3, 6, 9, 12–18 and 24 months after HCT and expressed as cumulative incidence considering death in remission as competing event.

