### Patients’ selection

Fifteen pediatric subjects will be enrolled in this study after obtaining informed consent. The study population will comprise any infant (1 month- 24 months), child (2–11 years) and teenager (12–18 years) affected by high-risk ALL or AML, candidate to an haplo-HCT and with an expected risk of leukemia relapse after transplantation ≥ 50% according to the available literature data. In **Tables 1**, **2** patients’ inclusion and exclusion criteria are reported, respectively. Eligible donors are HLA haploidentical relatives, including but not limited to biological parents, siblings, or half-siblings. Matching will be determined by class I and class II DNA typing. In **Table 3**, donor inclusion and exclusion criteria are reported.

**Table 1 T1:** Inclusion criteria for ALL and AML patients’ enrolment.

ALL patients’ inclusion criteria	AML patients’ inclusion criteria
Age ≥ 1 month and ≤ 18 years	Age ≥ 1 month and≤ 18 years
Life expectancy > 12 weeks	Life expectancy > 12 weeks
ALL in first morphological remission but with a positive MRD≥ 1 x 10–^3^ before HCT	AML in first morphological remission and with a flow cytometry MRD at the end of induction therapy ≥ 0.1%;
ALL in second morphological remission after a high-risk relapse (patients belonging to the S3-S4 BFM risk group), independently of the level of MRD	AML in first morphological remission and with high-risk disease according to the presence of unfavorable cytogenetic or molecular aberrations
ALL in second morphological remission with any MRD positivity before HCT	AML in first morphological remission after a primary induction failure
ALL in third or subsequent morphological remission, independently of the level of MRD	AML in second morphological remission
ALL patients not in morphological remission at time of HSCT	AML in third or subsequent morphological remission
Pre-HSCT Lansky/Karnofsky score ≥ 40%.	Pre-HSCT Lansky/Karnofsky score ≥ 40%.
HIV negativity	HIV negativity

**Table 2 T2:** Exclusion criteria for patients’ enrolment.

Patients’ exclusion criteria
Ongoing active acute GVHD or chronic GVHD due to a previous allograft
Presence of clinically active infectious disease (including positive HIV serology or viral RNA)
Severe cardiovascular disease (arrhythmias requiring chronic treatment, congestive heart failure or left ventricular ejection fraction <40%)
Liver dysfunction (AST/ALT ≥ 3 times institutional upper limit normal value –ULN- or bilirubin > 3 times ULN)

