### Sample size and data analysis

The sample size is calculated based on the primary safety endpoint, using the single stage method for phase II studies proposed by Fleming (35). This method has been primarily designed to provide sufficient clinical experience to support the design of later-stage clinical development such as phase III studies. We assumed a maximum proportion P0 of patients developing GVHD, for patients receiving the standard treatment (DLI), of 40% based on our previous experience, and on data reported in the literature (H0). We consider 10% as the maximum proportion P1 of patients developing GVHD for the study treatment (CTLs) to consider the study treatment for preliminary success (H1). A sample size of 15 patients (including a dropout of 1 patient) will be able to reject H0 with a power of 80% and a type I error of 5%. If the number of responses at the end of the study is ≤ 2, H0 will be rejected; if the number of responses is > 2, H1 will be rejected. Quantitative variables will be reported as the median value and range, while categorical variables will be expressed as absolute numbers and percentage. The demographic and clinical characteristics of patients and controls will be compared using the Chi-square test or Fisher’s exact test for categorical variables, while the Mann-Whitney rank sum test or the Student’s t-test will be used for continuous variables as appropriate. Overall survival (OS) and event-free survival (EFS) will be calculated according to the Kaplan-Meier method, while the risk of acute and chronic GVHD, relapse and death in remission, defined as non-relapse mortality (NRM) will be calculated as cumulative incidences (CI) in order to adjust the analysis for competing risks. Comparisons between different OS and EFS probabilities will be performed using the Log-Rank test, while the Gray’s test will be used to assess, in univariable analyses, differences between cumulative incidences. All results will be expressed as probabilities (%) or cumulative incidences (%) and 95% confidence interval (95% CI), at 3, 6, 9, 12, 18 and 24 months from HCT. P values < 0.05 will be considered statistically significant. Statistical analysis will be performed using NCSS [NCSS 10 Statistical Software (2015). NCSS, LLC. Kaysville, Utah, ncss.com/software/ncss.] and MP/15 (StataCorp LP, [name] (http://www.stata.com).

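### The primary objective is worded both as a one-sample test against 40% and as a comparison with DLI controls, and the stated 80% power belongs only to the first

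*Protocol article*

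**What the plan says.** The objective appears in two forms.

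- **Without a comparator.** Study objectives: "The primary objective will be safety, measured as the incidence of acute GVHD after treatment". Sample size and data analysis sizes the trial on the primary safety endpoint, "using the single stage method for phase II studies proposed by Fleming". The null value is fixed in advance: "We assumed a maximum proportion P0 of patients developing GVHD, for patients receiving the standard treatment (DLI), of 40" per cent, taken from the centre's experience and the literature. The alternative is: "We consider 10% as the maximum proportion P1 of patients developing GVHD for the study treatment (CTLs"). Fifteen patients, one of them an allowance for dropout, are said to give 80% power at a 5% type I error. H0 is rejected if the count is 2 or fewer. Sidedness is not stated.
- **With a comparator.** Discussion: "The primary objective is the incidence of acute GVHD compared with that observed in a control cohort of patients with identical characteristics", the cohort being DLI recipients. Trial design supports this: "The outcome of treated patients will be compared with that of pediatric recipients of haplo-HCT with the same disease characteristics and prognosis". The statistical section also lists Gray's test for differences between cumulative incidences, with significance at P < 0.05, and Study objectives expresses grade II-IV acute GVHD as a cumulative incidence.

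On numbers, Patients' selection says: "Fifteen pediatric subjects will be enrolled in this study after obtaining informed consent". The Figure 1 legend takes one study population and divides it: "Depending on the availability of cryopreserved LB patients will be assigned to the treatment with anti-leukemia CTLs (experimental arm"), with the rest going to DLI. The article gives no size for the DLI group and no power for a two-group comparison.

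**The concern.** These are different questions. One asks whether the GVHD rate in CTL patients is below a fixed 40%; the other asks whether it is below the rate seen in DLI patients treated alongside them. A sample size that answers the first need not answer the second. If the Discussion wording stands, the article states a primary objective to which its own power statement does not apply.

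What is at stake is the conclusion. P0 is described as a maximum for DLI, so rejecting it places the CTL rate below that ceiling and says nothing direct about the rate in the control cohort. A pass on the count could then be reported as lower GVHD than with DLI, a comparative safety claim in children that the test does not make.

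**Working it through.** **1. The plan's own figure.** Inputs from Sample size and data analysis: P0 = 0.40, P1 = 0.10, reject H0 if X ≤ 2, and 15 patients including 1 dropout, so 14 evaluable.

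P(X ≤ 2) = (1−p)^n + n·p·(1−p)^(n−1) + [n(n−1)/2]·p²·(1−p)^(n−2)

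- n = 14, p = 0.40: 0.0008 + 0.0073 + 0.0317 = 0.0398 (alpha)
- n = 14, p = 0.10: 0.2288 + 0.3559 + 0.2570 = 0.8416 (power)
- n = 15: alpha 0.0271, power 0.8159

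At n = 13 the rule X ≤ 2 has alpha 0.0579, and X ≤ 1 has power 0.6213. The smallest design meeting 5% and 80% is therefore n = 14, and one dropout gives 15. The stated figures reproduce as a one-sided, one-sample test. DLI patients do not enter the rule.

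**2. Power if the objective is the DLI comparison.** Assumptions: CTL 10%, DLI 40% (the plan's own rates) and 15 CTL patients. The number of controls is not in the article, so it is varied.

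- Fisher and uncorrected chi-square: exact enumeration, power = Σx Σy b(x; 15, 0.10)·b(y; n₂, 0.40)·1[test rejects at 5%].
- Gray's test: simulation with complete follow-up, patients without GVHD kept in the risk set to the end; 20,000 runs (8,000 with 100 controls).

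Two-sided 5%:

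| CTL v DLI | Fisher | Gray | Chi-square |
|---|---|---|---|
| 15 v 15 | 32.5% | 48.5% | 51.0% |
| 15 v 30 | 52.3% | 54.5% | 61.1% |
| 15 v 100 | 67.5% | 60.8% | 69.6% |

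Normal-approximation check at 15 v 15: SE under H0 = √(2 × 0.25 × 0.75/15) = 0.158; SE under H1 = √((0.09 + 0.24)/15) = 0.148; z = (0.30 − 1.96 × 0.158)/0.148 = −0.067; power 47%.

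One-sided 5% at 15 v 15 gives 46% (Fisher), 62% (Gray) and 66% (chi-square). With 100 controls, one-sided Fisher (73%) and Gray (78%) remain below 80%; only chi-square (82%) and the normal approximation (81%) pass it.

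Patients per arm for 80% two-sided power: (1.96 × √0.375 + 0.842 × √0.33)²/0.30² = 31.5, so 32. By Fisher enumeration it is 36, and with continuity correction 38.

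**3. What a pass on the count shows.** Suppose 2/15 CTL patients and 6/15 controls have GVHD, so that DLI sits exactly at 40%. The count rule rejects H0. For the comparison, Fisher's two-sided p is 0.21. Uncorrected chi-square gives z = 0.267/√(0.267 × 0.733 × 2/15) = 1.65, p = 0.10. A pass can therefore coexist with a between-group result that is not significant, even when DLI performs as assumed.

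**The case against.** The strongest reply is that the operative plan is coherent. Only one decision rule exists, the count of 2 or fewer; it is tied explicitly to the primary safety endpoint, and its error rates reproduce. Gray's test is listed for all cumulative incidences with no success criterion attached, and the comparative wording sits in a Discussion sentence without test or threshold. This stands in part: a reader might infer two rival primary decision rules, and the article does not support that. It does not remove the conflict over what the primary objective is, because Trial design plans the comparison that the Discussion calls primary.

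Other stronger readings also go too far:

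- *The trial has 33% power.* That is a two-sided Fisher test with an assumed 15 controls. The article names Fisher only for demographic and clinical characteristics; for cumulative incidences it names Gray's test, at about 49%.
- *The 15 patients are divided between the arms.* The Figure 1 legend read with Patients' selection invites this, but the sample size section uses 15 as the one-sample CTL count. The wording needs clarifying; it is not a basis for a power figure.
- *The 40% benchmark is wrong because DLI does better.* The Introduction says escalating DLI has come with less GVHD but gives no rate, and nothing shown says the controls receive such a schedule. Dependence on a fixed benchmark is a property of every single-arm design.
- *The planned 95% intervals contradict the one-sided rule.* Whether they do depends on the interval method, and reporting 95% intervals beside such a rule is common.

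**Conclusion.** The point holds as an inconsistency in the statement of the primary objective. The sample size is not miscalculated: for the one-sample test against 40% it is correct, with exact power of 82% to 84% and alpha of 2.7% to 4.0%. That power does not carry over to the comparison described in the Discussion. Given the plan's rates and an assumed 15 controls, two-sided power for the comparison is about 33% to 50% depending on the test. More controls do not rescue it in two-sided testing: with 100, it is about 61% to 70%.

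The control numbers are assumptions, and the Gray's test figures are simulated with complete follow-up. The conclusion that no variant examined at 15 v 15 reaches 80% does not depend on the choice of test or on sidedness. Low power does not make a DLI comparison improper; it means the comparison cannot carry the primary claim at this size.

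**What to change.** 1. Name one primary analysis: the one-sample test of acute GVHD in CTL-treated patients against 40%, one-sided 5%, H0 rejected at 2 or fewer events. State that the 80% power refers to this test alone.
2. Reword the Discussion sentence on the primary objective to match Study objectives.
3. In Trial design and the statistical section, label the DLI comparison of acute GVHD as secondary and descriptive, reported as an estimate with a confidence interval.
4. State in Patients' selection and the Figure 1 legend that the 15 are CTL patients and that DLI controls are additional.
5. Word success as a GVHD rate below 40%, not as less GVHD than DLI.

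This changes text only and adds no patients. The price is a less favourable claim: the trial no longer offers a powered statement of superiority over DLI. If that statement is wanted as primary, the comparison must be sized for it, at roughly 32 to 38 patients per arm for 80% two-sided power at 10% versus 40%.

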## Data Availability

The original contributions presented in the study are included in the article/supplementary material. Further inquiries can be directed to the corresponding author.
